Chronic pain is one of the most frequent chronic disorders and has the highest prevalence in people with low back pain (cLBP), which is the main cause of economic and financial loss in terms of cost per treatment and days of work lost [30]. In Europe, the prevalence of cLBP varies from country to country. In Italy the prevalence of cLBP is approximately 6% [31]. While there is a high level of knowledge of the peripheral and spinal neurological mechanisms of chronic pain, evidence about central changes is emerging [32]. Numerous studies on the central mechanisms of chronic pain refer to neurogenic (or neuropathic) pain [33] which appears to be related to thalamocortical patterns measured both by EEG [34, 35] and by fMRI [3, 36, 37]. Furthermore, chronic pain seems to be related to specific cerebral fluctuations [38]. Evidence suggests that different brain structures are responsible of central changes in subjects with chronic pain [39], in particular the anterior circuit of the insula thus the anterior insula and the anterior cortex of the cingulum [40]. However, authors suggested the predominance of the medial prefrontal cortex [41]. Moreover, Apkarian et al (2011) estimated that by analyzing the activity of the medial prefrontal cortex and insula it could be estimated the magnitude and duration of lumbar pain with a margin of error of 20% [41]. Furthermore, Malinen et al showed that subjects with chronic pain have a condition of activation of abnormal RSN, with a higher activity frequency on insula and on the anterior cingulate cortex [42]. Numerous types of interdisciplinary treatments, including manipulative therapies, have been proposed to improve clinical outcomes in patients with cLBP [43]. However, there is still little evidence of the possibility of changes in brain activity in subjects with chronic pain using manual therapies, for example with an osteopathic approach. The osteopathic model uses a system of manual evaluation of the patient, defined osteopathic analysis, in order to highlight the presence of somatic dysfunctions (codes M99.00-09 classes ICD10), that is body districts with mobility restriction. Osteopathy addresses somatic dysfunctions through appropriate manual methods (OMT), with the aim of normalizing them [44]. The manual analysis with osteopathic modality is addressed to the analysis of body movements in order to highlight the mobility limitations of the single joints. The objective of this study is to evaluate the effect of osteopathic treatment on functional connectivity and on insula activity and therefore of the anterior circuit of the SN, both in resting state and during an 'interoceptive awareness' - IA - (heart rate) or 'exteroceptive awareness' - EA - (time count) task in a sample of subjects suffering from cLBP. This could shed light on the central effect of manual treatment with osteopathic modality, laying the first bases for understanding neural mechanisms.

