
MATERIALS AND METHODS

PURPOSE OF THE STUDY

The main aim of the present randomized controlled two-arm and single-blind study is to evaluate the change in activation and connectivity of the anterior cortex of the insula and the medial prefrontal cortex between before and after the period of manual treatment with osteopathic modality. Secondary goals are:

I) to monitor the differences of activity and FC of the SN between the study group and the sham control;

II) to monitor the intra-group differences and the intergroup of activities and of the CF of the SN immediately after the first treatment;

III) to monitor the differences in activity of intra-group and inter-group RSN during the treatment period;

IV) to monitor the differences in the IA and EA both within and between groups;

V) to evaluate the DTI structural differences;

VI) to evaluate differences in terms of GABA concentration in the anterior insula by means of

MRS

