**OUTCOMES**

*Functional Magnetic Resonance (fMRI)*

Acquisitions will be performed with a 3T MR tomograph at ITAB. The following recordings will be made with fMRI:

1) baseline

2) immediately after the first session

3) After 1 month, or at the end of the treatment period

The sequences that will be used are:

1) Eco-planar weighs in T2 * for fMRI measurements with contrast Blood Oxygenation

Level Dependent (BOLD) and Pseudo-continuous Arterial Spin Labeling (pCASL) for the Brain blood flow (CBF) measurements

2) Diffusion tensor imaging (DTI) sequences for the study of structural connectivity.

3) Spectroscopy sequences for the measurement of GABA concentrations.

The anatomical target will be the anterior insula.

*fMRI task*

A standard method to evaluate interoceptive and exteroceptive awareness will be used. This method is based on a paradigm already experimented in previous studies [27, 29, 46, 47]. This consists of three independent conditions presented in causal order for 15-20 sec each. The three conditions are: a task for IA, one for EA and a resting state period. The task of AI is to count own heart beats. EA's task is to count the rhythm of a sound stimulus, a piece of music, received in headphone. The period of fixation consists of voluntarily reducing cognitive activities to a minimum.

All the stimuli will be distinguished by a specific symbol on the display, which will also control the time for each individual task. When the task is finished, the subjects will report on a "visual analogue scale" the number of heart beats or rhythm deriving from the task.

*Diffusion Tensor Imaging (DTI)*

Structural connectivity will be investigated using the DTI, focusing on possible changes after the treatment period.

*Timing of instrumental acquisitions*

The instrumental acquisitions will last 50 minutes and will be divided as follows:

1) 5 'anatomical acquisition in T1

2) 10 'MRS

3) 10 'BOLD resting state

4) 5 'pCASL

5) 10 'DTI

6) 10 'BOLD TASK

*Questionnaires*

Patients included in the study will have to answer the following questionnaires in relation to the various times:

At inclusion

• General questionnaire with the purpose of collecting information on the social demographic status, drugs used, pain location and previous treatments.

• Temperament Evaluation of the Memphis, Pisa, Paris and San Diego - Autoquestionnaire (TEMPS-A). Self-administered questionnaire that measures temperament.

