**STATISTIC ANALYSIS**

The lack of literature on precise estimate of the effect (effect size) of the manual treatment with osteopathic modality on the main outcome limits the calculation of the sample size. Therefore, given the lack of research measuring these effects at the brain level using fMRI, it is rather difficult to have a precise effect-size estimation. However, in general, the estimates reported in the literature for the expected effect-size with fMRI measures (eg comparison of connectivity values between different populations as in Greicius et al., 2007) indicate relatively high values (Cohen ‘s d= 1.01). This effect-size, together with an alpha and beta value of 0.05 and 0.8 respectively as usual in neuroimaging studies (Desmond et al., 2002) have been included in the R Statistical program to estimate the sample size, resulting in N=16 subjects per group.

Statistical analysis will be based on the 'intention-to-treat' and 'per-protocol' method. The statistical analysis will use the mean and standard deviation, median and percentiles, percentage points for the description of the variables of the two groups. The analyzes will be standardized by age and gender. The hypothesis H0 (null hypothesis) is the non-difference between the two groups at the end of the treatment. To test this hypothesis the assumption of the normal distribution of data through the Shapiro test will be tested first.

The analysis of residuals indicates the possible use of logarithmic transformations of the data. Subsequently the univariate analysis foresees the use of the analysis of the variance (ANOVA) for the comparison of the numerical variables, while the chi square (chi-square test) for the categorical and / or ordinal variables. Primarily used for the comparison of the two samples to the baseline, with the same method we will also analyze the data at the end of the treatment taking into account the inability to detect the independent effect of the variables on the outcome. ANCOVA will be used to explore in greater detail the treatment effect considering cofactors. Multivariate analysis will include the use of the best weighed model for confounding and interaction factors.

The level of statistical significance is established for an alpha <0.05. A post-hoc power calculation will be carried out.

Table 1. Exclusion criteria

• Subjects in acute phase,

• Subjects aged under 30 and over 50

• Associated co-morbidities (i.e. metabolic syndrome)

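### The main aim holds four unranked imaging quantities, while the plan sets one unadjusted 0.05 level and a sample size for a single two-group test

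*Protocol*

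**What the plan says.** The protocol's Purpose of the Study gives one main aim: "to evaluate the change in activation and connectivity of the anterior cortex of the insula and the medial prefrontal cortex", compared before and after the treatment period. That is activation and connectivity, each in two regions. Nothing ranks the four, combines them, or says whether one or all must be positive.

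The Statistic Analysis section has three relevant statements:

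- The sample size rests on one standardized effect; the cited fMRI estimates "indicate relatively high values (Cohen ‘s d= 1.01", used "together with an alpha and beta value of 0.05 and 0.8 respectively as usual in neuroimaging studies". The result is 16 subjects per group. The Randomization section plans 20 per group.
- One null hypothesis is given: "The hypothesis H0 (null hypothesis) is the non-difference between the two groups at the end of the treatment".
- One significance level is given for everything: "The level of statistical significance is established for an alpha <0.05". No adjustment, ordering or split of alpha is described.

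**The concern.** A 5% error rate for the main aim holds only if the aim is judged by one test, or by a rule that allows for several. Here the aim contains several candidate tests and no such rule. After the scans, an analyst could report whichever of the four fell below 0.05 as confirming the main aim and still be within the text. The headline claim would then carry a false-positive risk above the stated level.

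The sample size follows the same one-test logic. If a multiplicity correction were added later without naming a single primary measure, the planned numbers would no longer give 80% power, even at the large effect assumed.

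This goes beyond a correction method left to a later analysis plan. The contents of the main aim, the alpha and the sample size are all fixed in the protocol, and they do not match.

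**Working it through.** **Inputs.** From the Statistic Analysis section: d = 1.01, alpha 0.05, and 0.8, which is labelled beta but gives the stated size only if read as power. From the Randomization section: 20 per group. From the Purpose of the Study: 2 measures × 2 regions = 4 quantities. Assumed: two-sided testing (not stated) and a common correlation ρ between the quantities (not given, so shown as a range).

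**1. Reproduce the plan's figure.** For one two-sided comparison of two means,

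n = 2 × (1.960 + 0.842)² / 1.01² = 2 × 7.85 / 1.0201 = 15.4, so 16 per group.

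This matches the protocol. The t-test version gives 16.4. A one-sided test gives 13, which does not match. The sizing is therefore for one two-sided test at 0.05.

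**2. Chance of at least one false positive, all nulls true, each test at 0.05.** For k independent tests it is 1 − 0.95^k:

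- k = 4: 1 − 0.95⁴ = 18.5%
- k = 3 (connectivity read as the single insula–prefrontal link): 1 − 0.95³ = 14.3%
- k = 2 (one region only): 1 − 0.95² = 9.8%

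For equally correlated normal test statistics, the rate is 1 − ∫ φ(u) [Φ((1.96 − √ρ·u)/√(1−ρ)) − Φ((−1.96 − √ρ·u)/√(1−ρ))]^k du. With k = 4:

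| ρ | Rate |
|---|---|
| 0 | 18.5% |
| 0.3 | 17.4% |
| 0.5 | 15.6% |
| 0.7 | 13.0% |
| 0.8 | 11.4% |
| 0.9 | 9.4% |

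Simulated two-sample t-tests with 16 and 20 per group, for ρ from 0 to 0.8, agree within about 0.4 percentage points.

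**3. Power per test at d = 1.01 (two-sample t-test).**

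| Analysed per group | alpha 0.05 | alpha 0.05/4 = 0.0125 |
|---|---|---|
| 20 | 87.5% | 71% |
| 16 | 79% | 58% |

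At alpha 0.0125, 80% power needs 22 per group by the normal approximation, or 24 by the t-test (23.5 rounded up). The margin from 16 to 20 does not cover a four-way correction.

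**The case against.** The strongest reply is that the protocol contains no rule that any one positive result counts. It states one null hypothesis and one general alpha; that each quantity is tested at 0.05 is an inference. A multiplicity procedure may also sit in an analysis plan that is not at hand. This stands to the extent that the error rates must be stated as conditional. If all four had to be positive there would be no inflation, but the protocol does not say that either. The mismatch between a four-part aim and a one-test design remains.

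The second reply is that the size depends on a correlation nobody has given and on how the aim is counted. This stands too. A reader might take 13% as a lower bound, but that requires a correlation of about 0.7 or less, and counting two or three quantities also lowers the rate.

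Two stronger readings are tempting and not supported:

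- A reader might multiply the four quantities by three states (rest and two tasks) to reach twelve primary tests, because the introduction's objective speaks of activity "both in resting state and during an 'interoceptive awareness" and exteroceptive tasks. But the Purpose of the Study lists resting-state network differences and interoceptive and exteroceptive differences as secondary goals III and IV, and the introduction's sentence does not name the medial prefrontal cortex.
- A reader might infer that the Outcomes section contradicts the aim, since it says "The anatomical target will be the anterior insula". That sentence directly follows the spectroscopy item, and secondary goal VI places the GABA measurement in the anterior insula. It probably describes the spectroscopy target, so at most it needs clarifying.

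Finally, for a study of mechanism, cutting the main aim to one measure narrows the scientific question. That is a fair cost, and it is why a route that keeps all four is offered below.

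**Conclusion.** The point holds in a limited form. The protocol leaves four main-aim quantities unranked, with one unadjusted alpha and a sample size for one test. If success on any one would support the main aim, the false-positive chance is about 9% to 19% instead of 5%: roughly two to four times nominal. This assumes all nulls are true, two-sided tests at 0.05 and an equal correlation between 0 and 0.9. Narrower readings give at most 14.3% (three quantities) or 9.8% (two).

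The power figures assume a two-group contrast with all 20 per arm analysed. Neither is secure. The main aim is a before/after change, and the between-group salience-network difference is secondary goal I, whereas the null hypothesis compares groups at the end of treatment. The Patient Preparation section also excludes data from subjects who fell asleep, or may have, during recording.

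**What to change.** **Preferred.** In the main aim, name one primary measure, region, state, time point and contrast, tested at 0.05. This matches the one-test sample size, with about 87.5% power at d = 1.01 if all 20 per arm are analysed. Make the other main-aim quantities secondary, with Holm or false discovery rate control.

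**If all four stay primary.** State that Holm or Bonferroni applies across them, and restate the power: about 71% per test at alpha 0.0125 with 20 per arm.

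In either case, say in the Outcomes section whether the anatomical-target sentence refers to spectroscopy only.

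**Cost.** Text changes, with no added patients or scans. Under the preferred route only one imaging measure can carry the headline claim, and the main aim becomes narrower. Under the alternative the aim stays broad, but power falls below 80% even at the assumed effect.
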